### Randomization

2.5

The central randomization method will be adopted, and Chengdu Integrated TCM & Western hospital will be responsible for the central randomization and data management. The random code of each center is obtained according to the order of “random number assigned by central code” generated by SAS statistical software. The results of the random sequence will be hidden in opaque envelopes.

### Blinding

2.6

Because the interventions are different in each of the 3 groups, it is impossible to blind this study. Independent third parties will evaluate the patients and the study results.

### Eligibility criteria

2.7

#### Inclusion criteria

2.7.1

Participants who meet the following criteria will be included in the study: Adults aged 18 to 65 years who meet the diagnostic criteria for episodic CSU as specified in 2 different systems—the 2018 Chinese guidelines for urticaria and the 2017 European guidelines for urticaria (Table 1).^[1,14]^ They must also meet the TCM diagnostic criteria for blood deficiency and wind dryness syndrome (Table 2).^[31,32]^ Two designated attending TCM physicians will independently assess the participants to make this diagnosis.

**Table 1 T1:**

Western medicine diagnostic criteria for CSU.

**Table 2 T2:**
[figure not shown]
Diagnostic criteria for the TCM differentiation of blood deficiency and wind dryness syndrome.^[31,32]^.

Participants cannot have used any glucocorticoids, immunosuppressants, antihistamines, or other drugs within 1 month of beginning the study; and they cannot have had acupuncture for urticaria during the same time period. They must be free of any psychological or mental illness, have no communication barriers, and be able to sign the informed consent voluntarily and accept and comply with the treatment as specified in the protocol.

#### Exclusion criteria

2.7.2

Patients who meet the following criteria will be excluded from participation in the study: People with severe cerebrovascular disease or disease of the liver, kidneys, or other organs, or those with systemic diseases and malignant tumors; pregnant or lactating women, or women of childbearing age who plan to become pregnant during the study period; patients with comorbid infections, severe gastrointestinal symptoms, laryngeal edema, or other potentially life-threatening systemic symptoms. Patients who also have other concomitant itchy diseases, allergies, or scars constitution, or patients with induced urticaria will also be excluded.

#### Termination and withdrawal criteria

2.7.3

Patients who fail to comply with the requirements of the research protocol will be terminated from study participation. This included patients who do not use the study drugs as prescribed. Participants with serious adverse events, disease exacerbation, or serious complications will be terminated from study participation. Those who cannot comply with the clinical protocol or are lost to follow-up or die during the study period will be also be removed from the study.

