## Abstract

Chronic spontaneous urticaria (CSU) is a common dermatologic disease that seriously affects patient quality of life. The choice of therapy to control the disease and prevent its recurrence has always presented a difficult clinical issue. Previous studies have shown that traditional Chinese medicine is a safe and effective treatment for CSU. Recently, the temporal rhythms of CSU, a disease characterized by intermittent flares of active disease and periods of little or no disease, have attracted the attention of traditional Chinese medicine researchers. We designed a multicenter, randomized, controlled study to evaluate the efficacy and safety of combining a Chinese herbal formulation with acupuncture using shu-stream acupoints applied on the corresponding time meridians during disease exacerbations. We plan to recruit 111 outpatients with CSU aged 18 to 65 years. Participants will be randomized to 1 of the 3 groups: group A, which will be given basic acupuncture and the herbal formulation dangui yinzi; group B, which will be given danggui yinzi and shu-stream acupuncture; and a control group, which will be given danggui yinzi alone. Patients will be treated for 4 weeks and followed for 8 additional weeks. Investigators will evaluate the following parameters: the symptoms and side effects of treatment, quality of life (using the chronic urticaria quality of life questionnaire), and overall patient condition. Each week, patients will also complete the measurement of 7-day urticarial activity score. This is the first use of a combination of shu-stream acupoints and Chinese herbal medicine in the treatment of CSU. If successful, it will prove to be a simple, inexpensive, treatment strategy for solving a difficult clinical problem.

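### Section 2.7.3 ends study participation, not only treatment, for non-compliance and disease exacerbation, so follow-up is lost for reasons tied to the outcome and the comparison can be biased

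*Protocol article*

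**What the plan says.** Section 2.7.3 of the protocol article (Termination and withdrawal criteria) gives three groups of exit reasons.

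- Non-compliance: "Patients who fail to comply with the requirements of the research protocol will be terminated from study participation". On drug adherence it adds: "This included patients who do not use the study drugs as prescribed".
- Clinical events: "Participants with serious adverse events, disease exacerbation, or serious complications will be terminated from study participation".
- Patients who cannot comply, together with those who are "lost to follow-up or die during the study period will be also be removed from the study".

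The section does not distinguish a patient who stops study treatment from one who leaves the study. It provides for no measurement after termination.

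Four other places bear on the point:

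- Section 2.6 (Blinding): "Because the interventions are different in each of the 3 groups, it is impossible to blind this study". It adds: "Independent third parties will evaluate the patients and the study results". These assessors are not said to be masked or to decide who is terminated.
- Section 3.2.1 lists weekly UAS7, a sum of daily hive counts and itch severity, as a main efficacy index, alongside the CU-Q2oL quality-of-life questionnaire.
- The Abstract describes group B's acupoints as "applied on the corresponding time meridians during disease exacerbations", and section 3.1 ties their timing to predictable, rhythmic exacerbations.
- Section 3.3 records safety observations and laboratory results from enrolment through follow-up. The Abstract sets this at 4 weeks of treatment plus 8 weeks of follow-up, so to week 12.

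**The concern.** A randomised comparison is protected only while follow-up does not depend on how patients fare. Here two exit reasons are linked to the outcome. Exacerbation of urticaria is itself a high UAS7, and non-compliance may go along with poor response.

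Staff know each patient's arm, and the article gives no threshold for exacerbation or for failing to comply. Knowledge of the arm could therefore influence who leaves. Groups A and B also have acupuncture to comply with, on top of the herbal drug taken in all three arms. Even with an even-handed rule, if the treatments differ in effect, more patients will leave the weaker arm.

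What is at stake is the UAS7 and quality-of-life data after termination. A statistical analysis plan can define an all-randomised analysis set, but it cannot recover values that were never collected.

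**Working it through.** The plan gives no figure for the effect of this rule, so there is none to reproduce. The calculations below show what such a rule can do. All removal shares are assumptions, because the article states none. Each calculation also assumes that removed patients are the worst values or the failures and contribute nothing to the analysis, which is the upper end for a given share.

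**1. Continuous outcome, no true effect.** If the worst fraction p of a normally distributed outcome is removed, the mean of the rest improves by φ(z)/(1 − p) SD, where z cuts off the worst p.

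| Worst share removed | Shift in arm mean (SD) |
|---|---|
| 5% | 0.109 |
| 10% | 0.195 |
| 15% | 0.274 |
| 20% | 0.350 |

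- 20% against 5%: 0.350 − 0.109 = 0.241 SD.
- 20% against 10%: 0.350 − 0.195 = 0.155 SD (0.15 before rounding of the two terms).
- 15% against 15%: no expected difference.

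**2. Error rate.** The trial has 111/3 = 37 patients per arm (section 2.1). In a simulation of 10,000 trials with an unequal-variance t-test at two-sided 5% (sidedness assumed) and no true effect, values beyond the stated cut-off were removed.

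| Worst share removed, arm 1 / arm 2 | False-positive rate |
|---|---|
| 0% / 0% | about 5% |
| 15% / 15% | about 5% |
| 5% / 15% | about 12% |
| 5% / 25% | about 32% |

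**3. Response rates, real difference.** Section 2.4 plans on a lowest rate of 60% and a highest of 95%, a difference of 35 points. If a share q of failures is removed, the observed rate is r/(r + (1 − r)(1 − q)), where r is the true rate. With q = 50% in both arms:

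- weaker arm: 0.60/(0.60 + 0.40 × 0.5) = 0.750, with 0.40 × 0.5 = 20% of the arm removed;
- stronger arm: 0.95/(0.95 + 0.05 × 0.5) = 0.974, with 0.05 × 0.5 = 2.5% removed;
- observed difference: 97.4 − 75.0 = 22.4 points.

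With q = 25% the difference is 29.5 points, and with q = 75% it is 13.0 points. The same share of failures in each arm thus gives very unequal losses and hides part of a real effect.

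**4. Response rates, no real difference.** With 60% true response in both arms, removing 10% of failures in one arm and 30% in the other gives 0.60/(0.60 + 0.36) = 62.5% against 0.60/(0.60 + 0.28) = 68.2%, a false difference of 5.7 points. At 90% true response the false difference is 1.9 points. Removing the same share in both arms gives none.

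**5. Passages to reconcile.** Section 2.7.3 makes disease exacerbation an exit reason. The Abstract and section 3.1 use the same word for the recurring episodes that set the timing of group B's treatment. Section 3.3 records safety through follow-up, whereas section 2.7.3 ends participation for patients with serious adverse events and does not say whether that recording continues.

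**The case against.** The strongest reply is that section 2.7.3 governs participation, not analysis. It does not say that data already collected are discarded. UAS7 is recorded weekly, so scores up to termination, possibly including the week of worsening, may exist and could be analysed by assigned arm. This stands. A reader might infer that failures are dropped and only compliant non-failures are compared, but no passage specifies a completers-only analysis. What the text leaves uncollected is follow-up after termination. The article's silence on the analysis set is no fault in itself, since that is commonly left to the analysis plan.

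A reader might also infer that removal will be unequal across arms. The article does not say so. Its one example of non-compliance concerns the study drug, which all three arms take. It gives no acupuncture frequency from which to judge the extra burden, and non-adherent patients need not be the worst responders. Unequal removal is a well-founded risk, not a stated fact.

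Finally, it is tempting to read section 2.7.3 as contradicting the disease model by ending participation for the very flares that group B's treatment targets. In the list, exacerbation stands between serious adverse events and serious complications, which suggests overall serious worsening; the rhythms described elsewhere fall within a 24-hour period. Read as routine flares, the rule would terminate nearly everyone. This is an undefined term, not a demonstrated contradiction.

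None of this answers the central point: outcome-related exits end data collection, and later analysis cannot restore what was not collected.

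**Conclusion.** The point holds as a fault in a stated rule. After randomisation, in an open-label trial, participation ends for reasons related to the outcome and possibly to the arm, with no provision for later measurement. This can bias the comparison either way: unequal removal can create a false difference, and an even-handed rule can shrink a real one. Equal removal across equally effective arms would cause no bias.

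The sizes in the working, such as 0.15 to 0.24 SD with no true effect or 35 points falling to about 22, are illustrations and not forecasts. They rest on assumed removal shares and on the assumption that the worst patients go and contribute nothing. If scores before termination are kept and analysed, the effect would be expected to be smaller, but the loss of later follow-up remains.

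**What to change.** In section 2.7.3, separate stopping study treatment from leaving the study. Unless a patient withdraws consent, keep collecting weekly UAS7, CU-Q2oL and safety data to week 12 in every randomised patient, whatever the reason treatment stopped. State that these data are retained and analysed in the assigned arm.

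Reconcile the term disease exacerbation in section 2.7.3 with the rhythmic exacerbations in the Abstract and section 3.1. Reconcile section 2.7.3 with section 3.3 on whether safety recording continues after termination. When treatment is stopped remains a clinical decision and is not changed by this proposal.

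The cost is amendment wording and continued diaries, questionnaires and safety recording in patients who stop treatment. Their number cannot be read from the article.

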### Study drugs

2.8

The experimental drug is danggui yinzi, and it will be provided by Sichuan Neo-Green TCM in a granular formulation prepared by Smart TCM Pharmacy (Sichuan, China). Danggui yinzi contains the following ingredients:

(1)Angelica (dang gui) 10 g(2)Sheng (sheng di) 15 g(3)Salvia miltiorrhiza (chuang xiong) 15 g(4)Paeonia lactiflora (bai shao) 10 g(5)Radix astragali (huang qi) 15 g(6)Radix polygoni multiflori (fang feng) 10 g(7)Radix polygoni multiflori (zhi shou wu) 9 g(8)Tribulus terrestris (ji li) 10 g(9)Bombyx silkworm (jiang chan) 10 g(10)Glycyrrhiza (gan cao) 6 g

The herbs in the prescription are mixed and processed into a granular formulation and packaged into small, single-dose packs that will be distributed to the patients.

## Interventions

3

### Treatment plan

3.1

The 3 groups of patients, all diagnosed with blood deficiency and wind dryness syndrome according to the relevant TCM diagnosis and treatment guidelines, will take danggui yinzi mixed with about 150 mL of boiling water 3 times a day at 30 minutes after meals. Group A will also be administered with basic acupuncture as determined by a consensus of experts on the treatment of urticaria in TCM^[33]^: acupuncture Quchi (LI 11), Sanyinjiao (SP 6), and Xuehai (SP10). Group B will be administered shu-stream acupoints applied on the vigorous meridians of Qi and blood. According to accepted TCM theory, the shu-stream acupoints will be scheduled for specific times based on predictable, rhythmic disease exacerbations. For example, if CSU is active between 23:00 and 1:00, Zhlinqi (GB41), the shu-stream acupoints of the gallbladder meridian of foot-shaoyang will be applied.

### Outcome measures

3.2

#### Main efficacy index

3.2.1

Once a week, study participants will complete the measurement of 7-day urticaria activity score, which sums the daily hive count and itch severity recorded over 7 consecutive days.^[34]^ Quality of life will be evaluated using the chronic urticaria quality of life questionnaire.^[35]^

#### Secondary efficacy index

3.2.2

Investigators will score the patients’ main symptoms using the TCM guidelines for clinical research of new drugs.^[36]^ The overall evaluation of the patients’ condition will be evaluated using the visual analogue scale.

### Safety assessment

3.3

In China, Danggui yinzi has been used safely for more than 1000 years. The study dosage is the dosage recommended in the People's Republic of China Pharmacopoeia (2015 Edition). The acupuncture points selected for this study will all be located in the limbs. We will record any incidents of local hematomas, broken needles, residual needles, dizziness, unbearable acupuncture pain, severe pain after 1 hour, and local infection. In addition, to further evaluate the safety of this study, we will record the participants’ subjective observations and the results of laboratory tests, especially as they pertain to gastrointestinal intolerance and damage to the heart, liver, kidneys, and other organs from the time of enrollment through the follow-up period.

No matter whether the adverse events are related to the treatment methods of this study, they should be recorded in detail, including the occurrence time, symptoms, degree, duration, treatment methods and results, etc. In case of serious adverse events, the investigator must report to the clinical research responsible unit within 24 hours, and record it on case report form (CRF). At the same time, researchers will take necessary measures according to the condition and decide whether to stop the trial.

### Statistical analysis

3.4

Study data will be analyzed by experts from the Statistics Teaching and Research Office of Chengdu University of TCM, using statistical analysis software package SPSS 22.0. All data will be expressed in terms of mean ± standard deviation. If the sample data are distributed normally and the variance is uniform, the Student *t*-test will be used. The paired sample *T*-test will be used for intra-group comparisons, and the independent sample *T*-test will be used for inter-group comparisons. If the variance is not uniform, the approximate *T*-test will be used to compare the mean of the 2 independent samples. If the sample data are not normally distributed, the nonparametric rank sum test will be used. Pearson Chi-squared test will be used to count the data. Statistical significance will be set at *P* < .05.

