### Sample size calculation

2.4

The following formula was used to estimate the sample size with the ability to perform multiple sample rate comparisons^[27]^: 

According to the estimation of effective rate,^[28–30]^ the maximum and minimum estimated overall rate of TCM in the treatment of CSU are 95% and 60%, respectively. According to the above formula, the sample size for each group is 33. Thus, assuming that 15% of patients are likely to be lost during follow-up, a total number of study samples is determined to be 111 cases.

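### Section 3.4 compares three arms by two-sample t-tests at an unadjusted 5% level, with no joint test of means and two main indices: about 12% false-positive risk per index if all three pairs are tested

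*Protocol article*

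**What the plan says.** Section 2.1 of the protocol article allocates patients 1:1:1 to a control group or one of two treatment arms.

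Section 3.2.1 puts two measures under the main efficacy index. For UAS7: "Once a week, study participants will complete the measurement of 7-day urticaria activity score". For CU-Q2oL: "Quality of life will be evaluated using the chronic urticaria quality of life questionnaire". It does not say which of them decides, or whether success is needed on one or on both.

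For means, section 3.4 says that the independent-sample t-"test will be used for inter-group comparisons". If variances differ, an approximate t-"test will be used to compare the mean of the 2 independent samples". The other routes are given without saying how many groups enter: "If the sample data are not normally distributed, the nonparametric rank sum test will be used", and "Pearson Chi-squared test will be used to count the data". There is one threshold: "Statistical significance will be set at *P* < .05". Paired t-tests are named for changes within a group.

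Section 2.4 says its formula was used to "estimate the sample size with the ability to perform multiple sample rate comparisons", with rates of 95% and 60%.

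**The concern.** A two-sample t-test compares two arms, and this trial has three. Followed as written, the parametric route for the two main scores can only be a set of pairwise tests, each at .05. Nothing in section 3.4 limits how many of these may carry the conclusion: there is no joint test first, no order, no named contrast and no adjustment. With two main indices and three pairs, up to six between-arm tests stand side by side at one time point.

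At stake is the meaning of the stated threshold. A reader of the results would take P < .05 as a 5% risk of a false claim. The risk that some contrast crosses that line by chance is higher, and the trial is open-label (section 2.6) with no single contrast or index singled out in advance.

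**Working it through.** **Inputs from the protocol article.** Three arms, 1:1:1 (section 2.1); 33 per group before allowance for loss and 111 in total, so 111/3 = 37 per arm (section 2.4); two main indices (section 3.2.1); two-sample t-tests at .05 (section 3.4).

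**Assumptions.** Two-sided tests; no true difference between any arms; one time point per index. The article gives no correlation between UAS7 and CU-Q2oL, so 0 to 0.9 is shown. It states no family-wise error rate, so there is no figure of its own to reproduce beyond the .05 per test.

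**Step 1: one index, three pairs.** Some pair is significant when the largest difference between arm means exceeds 1.96 × √2 = 2.772 standard errors of an arm mean. For three groups, the studentized range gives P(range > 2.772) = 12.2%. Simulation of 100,000 null trials per setting, at 33 and 37 per arm, gives 12.0–12.4%. Treating the three tests as independent gives 1 − 0.95³ = 14.3%, which is too high because the pairs share arms.

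**Step 2: one index, two contrasts with control only.** The same simulation gives 8.8–9.2%.

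**Step 3: two indices, success on either.** At zero correlation the indices combine as independent:

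- three pairs: 1 − (1 − 0.122)² = 22.9%
- two control contrasts: 1 − (1 − 0.091)² = 17.4%

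Simulated at 33 and 37 per arm:

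| Assumed correlation | Three pairs | Two control contrasts | Three pairs, each index gated by its own F-test at .05 |
|---|---|---|---|
| 0 | 22.9–23.0% | 17.3–17.4% | 9.6–9.7% |
| 0.5 | 21.2–21.3% | about 16% | 9.1% |
| 0.7 | 19.5–19.9% | 14.9–15.0% | 8.4–8.6% |
| 0.9 | 16.8–16.9% | 12.6–12.8% | 7.1–7.2% |

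The independence formula for six tests, 1 − 0.95⁶ = 26.5%, is an upper reference only.

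**Step 4: two indices, success on both for the same contrast.** At zero correlation each contrast errs at 0.05² = 0.25%, so three contrasts give at most 0.75%. Simulation gives about 0.7% at correlation 0, rising to about 7.5% at 0.9.

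**Step 5: effect of a joint test.** If the pairwise tests are run only after a significant three-arm F-test at .05, the simulated error for one index is 4.9–5.1%. The gate is enough with exactly three arms. If all arms are equal, the F-test itself holds 5%. If one arm differs, only one true null pair remains, and it is tested at .05. The last column of the table shows that the gate alone does not suffice for two indices each at .05. At 0.025 per index the total is at most 0.025 + 0.025 = 0.05.

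**The case against.** The strongest reply is that the article gives no success rule. It does not name the contrasts, so perhaps only the two against control matter. It does not say that either index suffices; if both had to succeed on the same contrast, the error would be about 0.7–7.5%. This stands, and the 17–23% must therefore be read as conditional. It does not remove the problem, since even the two control contrasts on one index give about 9%.

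It can also be said that joint tests are available. The sample size is built on rates, the Pearson chi-squared test can be run on a three-arm table, and the rank sum test is not limited to two groups by the text. That is right, and a reader should not infer that section 3.4 rules out every joint test. The gap is in the route for means, where both the standard and the unequal-variance tests are two-sample.

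A third reply is that an analysis plan may settle this. Details of adjustment may well sit there. But the article fixes the test by name, and a later plan could provide a joint test of means only by departing from the published text.

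Two stronger readings are tempting and are not supported. Because UAS7 is completed weekly, a reader might infer that it is tested every week and the error multiplied accordingly; the article describes weekly collection, not weekly testing. A reader might also infer that a significant within-arm change counts as success. Section 3.4 names paired tests for intra-group comparisons but nowhere makes them a criterion for efficacy.

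**Conclusion.** The point holds in limited form. For means, section 3.4 commits a three-arm trial to two-sample t-tests at an unadjusted .05 with no joint test, and section 3.2.1 leaves open which of two main indices decides. Under no true effect and two-sided testing, the risk of at least one false positive is about 12% per index if all three pairs are tested, and about 9% if only the two control contrasts count. Over both indices it is about 17–23%, or about 13–17% for the two control contrasts. These last ranges apply only if success on either index is enough and for assumed correlations of 0.9 to 0. They are not the trial's established error rate, because the article states neither the contrasts nor the success rule. The per-index figures do not depend on the correlation.

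**What to change.** Amend section 3.4, and section 3.2.1 to match, before analysis:

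1. Test each main index first with a three-arm test at its allotted alpha: ANOVA or ANCOVA, Welch ANOVA if variances differ, Kruskal-Wallis if the data are not normal. Run the pairwise tests at that same level only if the three-arm test is significant. The 5% figure above was computed for the ANOVA route.
2. Settle the two indices in one of two ways. Either name one primary index and time point, chosen by the sponsor, and treat the other index as secondary without a confirmatory claim; or split alpha, 0.025 per index, with the same gate.
3. State that the within-arm paired tests are descriptive and are not evidence of a treatment effect.

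Simply opening CU-Q2oL once UAS7 is significant is not a substitute. When one arm truly differs on UAS7 and CU-Q2oL is null, simulated family-wise error is 7–10% if any UAS7 success opens it, and 6–9% if it is opened contrast by contrast.

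The cost is wording in the protocol and analysis plan. No patients, visits or data are added. The small downside is that an isolated pairwise P < .05 no longer counts as success, with a slight loss of nominal power.

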### Study design

2.1

This study is a multicenter, parallel-group, randomized controlled trial (RCT). The protocol was registered on May 3, 2020, in the Chinese Clinical Trial Registry as Clinical Trial No. ChiCTR2000032609. A total of 111 eligible participants will be enrolled and randomly assigned to the control group or 1 of the 2 treatment arms in a ratio of 1:1:1. Figure 1 shows the study registration schedule, interventions, and assessments. Figure 2 is a flow chart of the study.

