### Recruitment

2.3

The participants will be recruited from the public through Chengdu Integrated TCM & Western Medicine Hospital and 3 subcenters, including the Affiliated Hospital of Chengdu University of TCM, The First People's Hospital of Longquanyi District Chengdu, and Xinjin Hospital of TCM. Before signing informed consent forms, participants will be screened first, and be aware of all the details of the clinical trial and the potential risks.

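### Section 3.4 fixes unadjusted between-group tests, chosen by distribution checks on the trial data, so precision is lost and the effect measure can switch

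*Protocol article*

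**What the plan says.** Section 3.4 of the protocol article sets out a ladder of tests for continuous outcomes.

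- "If the sample data are distributed normally and the variance is uniform", Student's t-test applies: paired within groups, independent-sample between groups.
- "If the variance is not uniform", an approximate t-test replaces it.
- For the remaining case: "If the sample data are not normally distributed, the nonparametric rank sum test will be used".

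The section names no covariate, centre term or model. It does not say whether the between-group test is applied to post-treatment scores or to change from baseline. It does not mention UAS7 or CU-Q2oL by name, but section 3.2.1 makes both of them main efficacy measures, so the general rule covers them.

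Other sections describe information that the ladder does not use. On UAS7, section 3.2.1 says: "Once a week, study participants will complete the measurement of 7-day urticaria activity score". Section 2.3 recruits through "Chengdu Integrated TCM & Western Medicine Hospital and 3 subcenters", which makes four centres. Section 2.5 ties allocation codes to centres: "The random code of each center is obtained according to the order of" centrally generated random numbers. Section 2.1 has patients "randomly assigned to the control group or 1 of the 2 treatment arms in a ratio of 1:1:1".

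**The concern.** Two features of the ladder are weak, and both are written into the text rather than left open.

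First, a two-sample t-test or rank sum test has no place for a patient's starting score or centre. A baseline UAS7 usually predicts the later UAS7, and a model that includes it has a smaller residual variance. With about 33 patients per arm that matters, and some chance imbalance at baseline is to be expected.

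Second, the test is picked after looking at the trial's own distributions. The t-tests estimate a difference in means; the rank sum test compares ranks. Nothing in section 3.4 stops group A against control being reported as a mean difference and group B against control as a rank comparison, or UAS7 one way and CU-Q2oL the other. The results would then not be on one scale, and a reader could not know in advance what is to be estimated.

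**Working it through.** **Inputs**

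- Patients per arm: 33 before allowance for loss (section 2.4). That number is derived from response rates of 95% and 60%, not from UAS7 means. The formula is missing from the readable text and no power is stated, so it cannot be firmly reproduced. It is used here only as an arm size, and the point does not depend on how it was obtained.
- Significance level: 0.05 (section 3.4). Sidedness is not stated; two-sided is assumed.
- Correlation r between baseline and follow-up score: not given. Assumed range 0.3 to 0.7.
- SD of UAS7 and between-centre variance: not given. Effects are expressed in SD units, with equal SD at baseline and follow-up assumed.

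**Variance formulas (large samples)**

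Take the variance of the arm difference from post-treatment scores as 1. From change scores it is 2(1 − r). From ANCOVA it is 1 − r². Hence:

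- ANCOVA against post-treatment scores: ratio 1 − r², reduction r².
- ANCOVA against change scores: ratio (1 − r²) / [2(1 − r)] = (1 + r)/2, reduction (1 − r)/2.

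| r | Reduction against post-treatment scores | Reduction against change scores |
|---|---|---|
| 0.3 | 9% | 35% |
| 0.4 | 16% | 30% |
| 0.5 | 25% | 25% |
| 0.6 | 36% | 20% |
| 0.7 | 49% | 15% |

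Both reductions are positive for any r strictly between 0 and 1. The direction of the loss therefore does not depend on the assumed value; only its size does.

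**In patients.** Against post-treatment scores, 33 per arm with ANCOVA would be worth 33/0.91 = 36.3 at r = 0.3, 33/0.75 = 44.0 at r = 0.5 and 33/0.51 = 64.7 at r = 0.7. Against change scores the figures are 33/0.65 = 50.8, 33/0.75 = 44.0 and 33/0.85 = 38.8.

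**In power.** Take the effect that a post-treatment t-test with 33 per arm detects with 80% power: (1.960 + 0.842) × √(2/33) = 0.69 SD. This is an illustration, since the plan has no UAS7 target.

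| r | Post-treatment scores | Change scores | ANCOVA |
|---|---|---|---|
| 0.3 | 80% | 65.8% | 83.6% |
| 0.5 | 80% | 80.0% | 89.9% |
| 0.7 | 80% | 95.1% | 97.5% |

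**Chance imbalance.** The standard error of the baseline difference between two arms of 33 is √(2/33) = 0.246 SD. A difference beyond 0.3 SD in either direction has probability 2 × [1 − Φ(0.3/0.246)], about 22% per contrast. A post-treatment comparison carries r times that difference into the estimate. A change-score comparison carries −(1 − r) times it. ANCOVA removes the part that is linear in baseline.

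**Does choosing the test from the data inflate type I error?** The ladder was simulated under no effect with 33 per arm and 10,000 runs per setting. A normality test in each arm decided between rank sum and t, and a variance test decided between Student and approximate t. The rejection rate was 5.1% with normal data and 5.0% with scores rounded and clipped to 0 to 42. The simulation error is about √(0.05 × 0.95 / 10,000) = 0.2 percentage points. No inflation was seen in these settings.

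**Centre.** The article gives no between-centre variance, so the precision lost by omitting centre cannot be computed.

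**The case against.** The best defence is that unadjusted two-sample tests are valid under randomisation, and that covariates and repeated-measures models are often left to an analysis plan. Validity stands. The second part does not dispose of the point: section 3.4 is not silent but prescribes specific tests, and a later plan with a model would contradict it.

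Several stronger readings are tempting, and the document does not support them.

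- That baseline is ignored altogether. The text leaves open whether change scores are tested. A change-score t-test does use baseline, though less efficiently than ANCOVA.
- That a set fraction, such as a quarter, of the information is wasted. A quarter requires r = 0.5, which is nowhere stated, and it would cover baseline only.
- That t-tests are run week by week and lose patients with missing later weeks. Section 3.4 describes no weekly testing, and an article may leave the handling of missing data to the full protocol.
- That randomisation is stratified by centre, so that a centre term is obligatory. Section 2.5 says how each centre's codes are obtained but does not state stratification. A centre term is sensible in a four-centre trial; the text does not show that the design demands it.
- That choosing the test from the data raises the false-positive rate. The simulation above does not bear this out.

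It is also fair to say that a pre-treatment UAS7 is inferred from the paired tests. The schedule figure is not shown, so the baseline measurement cannot be confirmed from the readable text.

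**Conclusion.** The point holds as one of efficiency and of a fixed effect measure, not of validity. The prescribed between-group tests adjust for neither baseline nor centre, and the reported effect can be a mean difference or a rank comparison depending on checks of the trial data. Against ANCOVA, the avoidable variance is 9% to 49% if post-treatment scores are tested and 35% to 15% if change scores are tested, as r goes from 0.3 to 0.7. These sizes rest on the assumed r, on equal SD at both times for the change-score figures, on large-sample formulas, and on a baseline score being recorded. The switch of effect measure follows from the wording alone and needs no assumption. The change is worth making before the data are seen, but the trial's conclusions would not be invalid without it.

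**What to change.** In section 3.4, replace the ladder for UAS7 and CU-Q2oL with one prespecified baseline-adjusted model. A suitable form is ANCOVA at the end of the 4-week treatment period with arm, baseline score and centre, reporting each arm contrast as an adjusted mean difference with its confidence interval. For UAS7, a mixed model on the weekly scores with arm, week, arm by week, baseline and centre would serve as well, with the contrasts read at the same time point. Name one of the two in advance. If the full protocol designates another time point, use that one.

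Handle unequal variances or skewed residuals with robust standard errors rather than by changing the test, and keep the rank sum test as a sensitivity analysis only. State that a pre-treatment UAS7 and CU-Q2oL are recorded for every patient.

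The cost is a change of wording and slightly more analysis work. SPSS 22.0, which section 3.4 already names, can fit these models. No extra patients are needed, and no extra data if the baseline scores are recorded as the paired tests imply.
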